### Randomisation

Potentially eligible children will be identified from the electronic databases of practices or in the case of practices without a computer by the Business Services Organisation. These children will be block-booked into dedicated trial sessions in the dental practices. A separate randomisation schedule will be prepared by the CRSC for each recruiting centre using randomised permutated blocks. The block lengths will vary to ensure the centres are blind to patient allocation. An invitation letter and trial information leaflet will be sent to parents of identified children asking if they would like to participate in the trial. An appointment for a check-up will be included in the invitation and will stress that the adult with parental responsibility for the child must accompany the child when they attend for assessment. The child's dentist or the external dental examiners (who will undertake the baseline examinations) will consent the children into the trial. Baseline assessment will be undertaken after each child has been consented but prior to randomisation.

An eligibility form will be faxed to the CRSC, where the children will be centrally randomised to one of the two treatment groups. The children will initially be identified at registration by their initials, date of birth and gender only. Once all of the eligibility criteria have been verified by the CTU they will provide the investigator with confirmation of the treatment allocation via fax to provide a paper record of the allocation, and the unique patient ID will be assigned.

### Sample size considerations

The principal outcome measure is whether the child develops caries in the primary dentition or not. We expect to see an absolute difference in the proportion of children with caries after 3 years of 0.1 between test and control groups. If caries free children are selected for the study it is estimated that 47% will develop caries over the three years. A two group chi-square test with a 0.050 two-sided significance level will have 90% power to detect the difference between a proportion of 0.470 and a proportion of 0.370 (odds ratio of 0.662) when the sample size in each group is 510. We assume that 2% will be excluded because of a history of severe allergic reaction and a further 1% for other reasons. We also assume that 75% of children approached will be caries free and a 70% consent rate with an estimated 15% drop-out rate over the 3 years. Therefore we will need to initially invite at least 2,356 children to take part in the study, recruiting 1200 children to ensure we have sufficient power at the end of the trial. The recruitment process is summarised in the CONSORT flow chart in Figure 3.

**Figure 3 F3:**
[figure not shown]
**CONSORT flowchart showing the estimated numbers of children throughout the trial**.

### Statistical analysis

All analyses will use an 'intention to treat' principal. All outcome measures stated in the protocol will be fully analysed using generalized linear models adjusting for covariates felt to be of prognostic importance including age and socio-economic status (SES). Statistical significance will be at the 0.05 level for all analysis and 95% confidence intervals will be calculated. A binary logistic regression model will be fitted to the primary outcome, whether the child remained caries free or not, with study group, age and socioeconomic status as covariates. The unadjusted and adjusted odds ratios from the logistic regression model will be reported and will specify that the adjusted is the primary analytical approach. A pre-planned subgroup analysis will be undertaken for deprived/not deprived children by selecting children whose parents are exempt from dental charges or not.

Health economic analysis will compare the total cost to the NHS for dental care in each of the two arms of the trial in accordance with the relative levels of effectiveness for each of the two arms. A multiple linear regression model will be fitted to the individual discounted costs per child with group, age and socio-economic status (SES) as covariates. If the assumptions underlying the model are not upheld, robust estimates of the standard errors will be calculated for the estimated parameters. Separate calculations will be made of between-treatment differences in cost to parents to identify any between-programme trade-offs. All calculations will be subjected to sensitivity analysis and discount rates of 3.5% for both cost and benefits will be applied. The incremental cost effectiveness ratio (ICER) will be estimated by dividing the difference in mean discounted costs between the two groups by the difference in discounted proportions that remain caries free. The relationship between cost and secondary outcomes such as the number of carious surfaces will be examined in an analogous fashion to that detailed above. The net present value of costs will be divided by the net present value of the number of carious surfaces to ascertain the average cost for carious surface avoided.

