**Methods/Design:**

A randomised controlled trial on children initially aged 2 and 3 years old who are regular attenders at the primary dental care services in Northern Ireland. Children will be recruited and randomised in dental practices. Children will be randomised to the prevention package of both fluoride varnish (twice per year for three years), fluoride toothpaste (1,450 ppm F) (supplied twice per year), a toothbrush (supplied twice a year) or not; both test and control groups receive standardised dental health education delivered by the dentist twice per year. Randomisation will be conducted by the Belfast Trust Clinical Research Support Centre ([CRSC] a Clinical Trials Unit).

1200 participants will be recruited from approximately 40 dental practices. Children will be examined for caries by independent dental examiners at baseline and will be excluded if they have caries. The independent dental examiners will examine the children again at 3 years blinded to study group.

The primary end-point is whether the child develops caries (cavitation into dentine) or not over the three years. One secondary outcome is the number of carious surfaces in the primary dentition in children who experience caries. Other secondary outcomes are episodes of pain, extraction of primary teeth, other adverse events and costs which will be obtained from parental questionnaires.

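### Randomisation is stratified by dental practice but the primary and cost models omit practice, so the primary test is mildly conservative if practices differ; the planned 90% power is still met

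*Protocol article*

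**What the plan says.** The Randomisation section states: "A separate randomisation schedule will be prepared by the CRSC for each recruiting centre using randomised permutated blocks". The Methods/Design paragraph of the abstract identifies the centres as practices: "Children will be recruited and randomised in dental practices", and "1200 participants will be recruited from approximately 40 dental practices". Allocation is therefore individual and stratified by practice, with about 1200/40 = 30 children in each.

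The Statistical analysis section names a binary logistic regression for the primary outcome "with study group, age and socioeconomic status as covariates". Unadjusted and adjusted odds ratios are both to be reported, and the plan "will specify that the adjusted is the primary analytical approach". For costs: "A multiple linear regression model will be fitted to the individual discounted costs per child with group, age and socio-economic status (SES) as covariates". Practice is in neither model, and no practice-stratified test or practice-clustered standard error is named. Robust standard errors are offered for costs only if model assumptions fail, and without reference to practice.

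The sample size has no practice term either: "A two group chi-square test with a 0.050 two-sided significance level will have 90% power" for 0.47 against 0.37 with 510 per group.

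**The concern.** Blocking within practice removes between-practice differences in caries risk from the comparison of the arms. A model without practice still counts those differences as random error. Its standard error then describes a trial in which practice mix could differ by chance between arms, which this design largely prevents. The interval covers somewhat more than 95% of the time and the test rejects somewhat less than 5% of the time under the null.

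At stake is some precision that the design has already secured, in the analysis that the plan itself makes primary. The linear cost model has the same mismatch.

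**Working it through.** **1. The plan's own figure.** Inputs from Sample size considerations: 0.47 and 0.37, two-sided 0.05, 90% power.

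n = [1.960·√(2·0.42·0.58) + 1.282·√(0.47·0.53 + 0.37·0.63)]² / 0.10² = (1.368 + 0.890)² / 0.01 ≈ 510 per group. Then 1020/0.85 = 1200 recruited. Both stated figures reproduce. About 1020/40 ≈ 26 evaluable children per practice remain, 13 per arm.

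**2. Approximate formula.** With balance within practice and a common effect, the true SE is about the unstratified SE times f = √(1 − ICC), where ICC is on the observed (probability) scale. The documents give no ICC, so it is assumed over a range. With n = 510 per arm:

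- SE under the null: √(2·0.42·0.58/510) = 0.03091. SE under the alternative: √((0.2491 + 0.2331)/510) = 0.03075.
- Type I error without practice: 2[1 − Φ(1.96/f)].
- Power without practice: Φ[(0.10 − 1.96·0.03091)/(0.03075·f)].
- Power with practice: Φ[(0.10 − 1.96·0.03091·f)/(0.03075·f)].

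Example at ICC 0.10, f = 0.9487: type I error 2[1 − Φ(2.066)] = 3.9%; power Φ(1.351) = 91.2% without practice and Φ(1.458) = 92.8% with it.

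| Observed-scale ICC | SE overstated by | Type I error | Power without practice | Power with practice |
|---|---|---|---|---|
| 0 | 0% | 5.0% | 90.0% | 90.0% |
| 0.01 | 0.5% | 4.9% | 90.1% | 90.3% |
| 0.05 | 2.6% | 4.4% | 90.6% | 91.4% |
| 0.10 | 5.4% | 3.9% | 91.2% | 92.8% |

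**3. Simulation.** 40 practices, 15 per arm in each, 15% drop-out, normal practice intercepts on the logit scale, 20,000 replicates. The unstratified log-odds-ratio Wald test is compared with a Cochran-Mantel-Haenszel test stratified by practice. Latent ICC = s²/(s² + π²/3); for s = 0.75 this is 0.5625/(0.5625 + 3.290) = 0.15.

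| Intercept SD s | Latent ICC | Observed ICC | Model SE / true SD | Type I error, unstratified | Power, unstratified | Power, stratified |
|---|---|---|---|---|---|---|
| 0 | 0 | 0 | 1.00 | 5.1% | 90.0% | 89.8% |
| 0.35 | 0.04 | 0.029 | 1.01–1.02 | 4.5% | 90.4% | 90.9% |
| 0.50 | 0.07 | 0.056 | 1.02–1.03 | 4.45% | 90.4% | 91.2% |
| 0.75 | 0.15 | 0.111 | 1.05 | 3.9% | 91.0% | 92.9% |

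The stratified test holds its level (4.8% to 5.2%) in all four rows. Further runs with 13 per arm per practice gave unstratified type I errors of about 4.8% at latent ICC 0.05, 3.9% to 4.2% at 0.10 and 3.7% at 0.15. Power was 91.1% against 92.3% at 0.10, and 91.7% against 93.3% at 0.15.

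**4. What a random intercept does to the reported estimate.** Simulated mixed logistic fits at latent ICC 0.10 (800 trials) gave a mean log odds ratio of −0.418 without practice and −0.453 with it, and mean reported SEs of 0.1267 and 0.1321. The ratio of estimate to SE goes from 0.418/0.1267 = 3.30 to 0.453/0.1321 = 3.43. The gain appears in the test statistic, while the reported SE on the log-odds-ratio scale rises.

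**The case against.** Several points on the other side stand.

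- **Power.** A reader might infer that the trial falls short of its planned power. It does not: every figure above for the model without practice is at or above 90%. What is given up is extra power.
- **False positives.** A reader used to cluster trials might infer that ignoring practice inflates type I error. Here children are randomised within practice, so the error goes the other way.
- **Standard errors.** A reader might expect the fix to narrow the reported interval for the log odds ratio. Step 4 shows that it can widen. The standard error is too large only relative to the true sampling SD of the practice-unadjusted estimate.
- **Residual variation.** The Background section speaks of geographical and social inequalities across the UK. It says nothing of differences between practices in Northern Ireland among children selected as caries-free, and it links those inequalities to deprivation, which the SES covariate may partly absorb. The relevant ICC is what remains after age and SES, and it could be near zero.
- **Match to the planned models.** The main calculations compare unadjusted and stratified tests, not the exact planned and proposed regressions. They indicate size only.
- **Costs.** A larger loss for costs may seem likely if dentists differ in how they treat, but the documents give no figure from which to calculate it.

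One objection is weaker. The general covariate sentence is open-ended and an analysis plan may exist. But the sentence on the primary model lists its three terms and the protocol makes that adjusted model primary, so adding practice later would depart from the stated model.

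**Conclusion.** The mismatch between design and analysis is real and its consequence modest. For an assumed residual latent ICC of 0 to 0.15, type I error falls from about 5% to about 3.7%, and between 0 and about 2 points of attainable power are forgone. Nothing is lost if practices do not differ after age and SES.

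This rests on an assumed ICC, on equal allocation within practices of similar size, and on a treatment effect common to all practices. Each practice's own dentist delivers varnish and education, so the last assumption could fail, and the conservative direction is then not assured. The validity of the primary conclusion is not threatened. The change is worth making because it is nearly free and aligns the analysis with the randomisation.

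**What to change.** Add practice to the primary model, either as a random intercept alongside group, age and SES or through a practice-stratified or conditional analysis. Add it likewise to the cost regression and the count models, and report the models without practice as sensitivity analyses. Fix this before outcome data are seen by arm.

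The cost is one term per model and no new data, since practice is known for every child. The primary odds ratio becomes conditional on practice: it moves slightly away from the null, its log-scale SE may be larger, and the report should say so. The linear cost difference keeps its meaning. If practices turn out not to differ, the loss is negligible (89.8% against 90.0% power in the simulation with ICC 0).

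### The deprivation subgroup analysis is described as selecting subsets and names no group-by-exemption interaction, so as written it does not show whether the effect differs by deprivation

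*Protocol article*

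**What the plan says.** All of this stands in the Statistical analysis section of the protocol article, apart from the design figures.

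- The subgroup analysis is specified in advance, on one factor with two levels, and the same sentence gives the means, which is selection by exemption status: "subgroup analysis will be undertaken for deprived/not deprived children by selecting children whose parents are exempt from dental charges or not".
- The error level is general: "Statistical significance will be at the 0.05 level for all analysis and 95% confidence intervals will be calculated".
- The primary outcome is analysed by binary logistic regression "with study group, age and socioeconomic status as covariates". No product of study group and exemption is listed.
- Under Sample size considerations, the design figures are: "A two group chi-square test with a 0.050 two-sided significance level will have 90% power" for "a proportion of 0.470 and a proportion of 0.370 (odds ratio of 0.662"), "when the sample size in each group is 510".

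The article gives neither the expected share of exempt families nor any guide to interpreting the subgroup results.

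**The concern.** Whether the package works better or worse in deprived children is a question about the difference between two treatment effects. Two p-values, one from each subset, do not test that difference. Each depends on the size of its subset as well as on the effect in it, so one can fall below 0.05 and the other above it when the two effects are identical.

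This comparison is likely to be acted on. The Background ties caries closely to social deprivation. It also says that the Department of Health in Northern Ireland wants the trial's outcomes to inform the preventive part of a new dental contract. A report that the package works in only one of the two groups could be used to target it or to withhold it.

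**Working it through.** **Inputs from the article.** Control proportion 0.47, test proportion 0.37, two-sided alpha 0.05, 90% power, 510 analysed per arm, 15% drop-out, 1200 recruited.

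**Assumptions, not in the article.** The smaller subgroup holds 20% to 50% of the children, split equally between the arms. The planned proportions hold in both subgroups. Each subset is tested with an unadjusted two-proportion test, as a stand-in for the adjusted logistic model.

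**1. Reproduce the plan's own figure.** With mean proportion 0.42 and pooled variance:

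n = [1.96 × √(2 × 0.42 × 0.58) + 1.2816 × √(0.47 × 0.53 + 0.37 × 0.63)]² / 0.10² = 509.9, so 510 per arm.

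Drop-out: 1020 / 0.85 = 1200. Both stated figures are confirmed, and power at 510 per arm is 0.900.

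**2. Power within a subgroup of n per arm.**

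power = Φ{[0.10 × √n − 1.96 × √(2 × 0.42 × 0.58)] / √(0.47 × 0.53 + 0.37 × 0.63)}

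For n = 255: Φ(0.329) = 0.629.

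**3. Chance that exactly one subgroup is significant.** The subgroups contain different children, so with powers a and b the chance is a(1 − b) + b(1 − a). At 50/50: 2 × 0.629 × 0.371 = 0.467. At 20/80: 0.303 × 0.174 + 0.826 × 0.697 = 0.628.

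**4. Power of the interaction test.** The variance of a log odds ratio with n per arm is v(n) = 1/(n × 0.47 × 0.53) + 1/(n × 0.37 × 0.63). The standard error of the difference between two log odds ratios is √[v(n₁) + v(n₂)]. The main log odds ratio has absolute size |ln 0.662| = 0.412. At 50/50 the standard error is √(0.0326 + 0.0326) = 0.255, and power for an interaction of 0.412 is Φ(0.412/0.255 − 1.96) = 0.365. The ratio of odds ratios detectable with 80% power is exp(2.80 × SE).

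| Split | n per arm | Power in each subgroup | Exactly one significant | Interaction power (size 0.412) | Detectable ratio of odds ratios, 80% power |
|---|---|---|---|---|---|
| 20/80 | 102 / 408 | 0.303 / 0.826 | 0.628 | 0.252 | 2.44 |
| 25/75 | 128 / 382 | 0.367 / 0.801 | 0.580 | 0.288 | 2.28 |
| 30/70 | 153 / 357 | 0.425 / 0.774 | 0.541 | 0.316 | 2.18 |
| 40/60 | 204 / 306 | 0.535 / 0.709 | 0.486 | 0.353 | 2.07 |
| 50/50 | 255 / 255 | 0.629 / 0.629 | 0.467 | 0.365 | 2.04 |

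**5. Simulation, 200,000 trials per split, same effect in both subgroups.** Exactly one subgroup was significant in 57.9% (25/75) and 46.3% (50/50) of trials, in line with step 3. The interaction test was significant in 5.1% and 5.0%. Among trials with exactly one significant subgroup, the interaction was significant in only 7% (25/75) and 10% (50/50).

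**6. Unequal baseline risk.** Now let the control proportion in one subgroup be 0.60, with the other set so that the overall control proportion stays at 0.47, and keep a common odds ratio of 0.662. With the 0.60 subgroup holding 20%, 25%, 30%, 40% and 50% of children, the chance of exactly one significant subgroup is 0.622, 0.574, 0.535, 0.486 and 0.483. The picture hardly changes.

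**The case against.** The strongest reply is that the article gives this analysis one sentence, and that the phrase about selecting children may only define who counts as deprived. A journal article often leaves the form of a subgroup model to the full protocol or the analysis plan, which are not at hand. The 0.05 sentence is general and would cover an interaction test just as well. The article also promises 95% confidence intervals, which would help a careful reader see that two subgroup effects overlap. The subgroup factor is single, binary and chosen in advance, so multiplicity is a small matter.

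Much of this stands. A reader might infer that the protocol commits to separate tests with no interaction test, or that it will claim a differential effect whenever one subgroup reaches 0.05 and the other does not. The article supports neither. It never says in words that each subgroup is tested on its own, it does not exclude an interaction test, and it sets no rule for claiming that effects differ. The 47% to 63% is the chance of a misleading pattern under stated assumptions, not the chance that the investigators make a false claim.

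The reply does not remove the point. Selection of subsets is the only subgroup method that the article gives, and it stands next to a 0.05 rule for all analyses and a covariate list without the interaction. Someone following that text would run two subset analyses, so the criticism rests on a stated method and not only on a missing detail.

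**Conclusion.** The point holds in a limited form and is a cheap improvement. As worded, the deprivation analysis leads naturally to two subset analyses, which cannot show whether the effect differs by deprivation. With an identical true effect in both groups, one subgroup alone would be significant in about 47% to 63% of trials, against about 5% for a false-positive interaction. The low end, 47%, belongs to the most favourable split, so the conclusion does not depend on where in the assumed range the exempt share falls. The figures rest on the assumed share, on the planned effect being true in both subgroups, and on an unadjusted test. The primary analysis and the sample size are unaffected.

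**What to change.** Replace the subset analysis with the primary logistic model fitted to all children, adding exemption status and a group-by-exemption interaction. Report the interaction estimate with its 95% confidence interval and p-value. Take the effects in exempt and non-exempt children, with confidence intervals, from that model and present them as descriptive. State that any claim of a differential effect rests on the interaction only.

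The cost is a sentence or two, with no extra data and no change to recruitment. If the full protocol or analysis plan already says this, only the published wording needs to be brought into line. The drawback is the low power of the interaction test, about 25% to 37% for an interaction as large as the main log odds ratio. It will often be inconclusive, and the plan should say so in advance.

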### Outcome measures

Baseline and outcome examinations at 3 years will be performed by trained and calibrated examiners. Outcome examiners will be blinded to the treatment allocation and using the same diagnostic protocol. The primary outcome is to measure whether the child has become caries active (caries into dentine). The following secondary outcomes are to be measured on the children: the number of carious surfaces (caries into dentine) in the primary dentition for children who have become caries active, the number of episodes of pain and number of extractions of primary teeth and the costs of dental care over a 3 year period. The final three outcomes will be assessed by questionnaire filled in by the person with parental responsibility.

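### The formula for the cost per carious surface avoided divides cost by surfaces present, contradicting its own label and the incremental ratio defined just before it

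*Protocol article*

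**What the plan says.** Three consecutive sentences in the protocol article's Statistical analysis section bear on this point.

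1. The main incremental cost-effectiveness ratio (ICER) is obtained by "dividing the difference in mean discounted costs between the two groups by the difference in discounted proportions that remain caries free".
2. Secondary outcomes are then covered: "The relationship between cost and secondary outcomes such as the number of carious surfaces will be examined in an analogous fashion to that detailed above".
3. A specific formula follows, in which the net present value of costs is "divided by the net present value of the number of carious surfaces to ascertain the average cost for carious surface avoided".

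Just before these, the section says that "discount rates of 3.5% for both cost and benefits will be applied". The Outcome measures section defines the surface outcome as "the number of carious surfaces (caries into dentine) in the primary dentition for children who have become caries active".

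**The concern.** A surface avoided is never observed in any child. It exists only as a contrast: surfaces in the control arm minus surfaces in the test arm. A formula whose denominator is the number of carious surfaces cannot produce a cost per surface avoided, whichever arm or pool of children it is applied to.

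The second sentence points an analyst to a difference over a difference, and the third to a simple quotient. Both could be reported under the same label with very different values. What is at stake is one secondary economic result, in a trial for which comparing the costs of dental care is a stated objective.

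**Working it through.** **What can be checked.** The article gives no numerical cost per surface, so there is no figure to reproduce. The check compares the written formula with the incremental one.

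**Notation (per child).** C0, C1 are mean costs and S0, S1 mean carious surfaces in control and test.

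- As written: C/S, within an arm or pooled.
- By analogy with the ICER: (C1 − C0)/(S0 − S1).

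**Direction, if the cost term is an arm total.** Let cost be a + b·S, where a is the part that does not vary with surfaces and b is the treatment cost per surface. Then C/S = a/S + b. With a > 0 this rises as S falls. In the test arm a > 0 is realistic, because the Trial interventions section gives varnish, toothpaste and toothbrush to every test child.

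**Illustration.** All inputs are assumptions in arbitrary units, none from the article: S0 = 3.0; other fixed cost 100 per child; package cost 60; b = 20. Control: C0 = 100 + 20 × 3.0 = 160, and 160/3.0 = 53.

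| Reduction in surfaces | S1 | C1 = 160 + 20·S1 | Written, test arm C1/S1 | Written, pooled (C0+C1)/(S0+S1) | Incremental (C1−C0)/(S0−S1) |
|---|---|---|---|---|---|
| 10% | 2.7 | 214 | 79 | 66 | 180 |
| 20% | 2.4 | 208 | 87 | 68 | 80 |
| 40% | 1.8 | 196 | 109 | 74 | 30 |
| 60% | 1.2 | 184 | 153 | 82 | 13 |
| 80% | 0.6 | 172 | 287 | 92 | 5 |

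Treatment cost falls with surfaces here, so the pattern does not come from holding test-arm cost fixed.

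**Range over cost assumptions (test arm, 10% to 80% reduction).**

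- Other fixed cost 0, b = 20: written ratio 42 to 120; incremental 180 to 5.
- Other fixed cost 100, b = 0: written 59 to 267; incremental 200 to 25.
- Other fixed cost 100, b = 60: written 119 to 327. At 40% reduction, C0 = 280 and C1 = 160 + 60 × 1.8 = 268, so the package costs less and leaves fewer surfaces. The written ratio is nevertheless 149 in test against 93 in control.

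**Direction, if the cost term is incremental cost.** With package cost p, C1 − C0 = p − b(S0 − S1), so (C1 − C0)/S1 = b + (p − b·S0)/S1. This rises, stays flat or falls as S1 falls according to whether p is above, equal to or below b·S0. With p = 60 and S0 = 3.0 the turning point is b = 20. From 10% to 80% reduction the quotient goes from 22 to 100 at b = 0, stays at 20 at b = 20, and goes from 16 to −140 at b = 60. The denominator is still surfaces present in every case.

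**Which children form the mean.** Take the 47% and 37% from Sample size considerations and assume 5 surfaces per affected child in both arms. Among affected children the difference is 5 − 5 = 0. Over all children it is 0.47 × 5 − 0.37 × 5 = 2.35 − 1.85 = 0.50 surfaces avoided per child. Turning the formula into a difference therefore works only if the means cover all children, with caries-free children counted as zero.

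**The case against.** The best defence is that this is loose drafting. The preceding sentence promises an analogous approach, and the word avoided implies a contrast, so the authors probably meant the incremental ratio and left out the differences. That is a likely account of how the sentence arose. It does not remove the problem: the specific formula comes after the general promise, uses different terms, and is corrected nowhere else in the article.

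Other limits stand:

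- A reader might infer that the plan divides total cost by surfaces. The sentence speaks only of the net present value of costs. Arm totals are a fair reading because no difference is stated, but incremental cost is possible.
- A reader might infer that the ratio must worsen as the package works better. That follows only for arm-total costs with a component that does not scale with surfaces. Under the incremental reading the direction depends on treatment cost per surface.
- A reader might infer that contract decisions would rest on this figure. The Background says the Department of Health in Northern Ireland wants to use the trial's outcomes for the new contract, but nothing ties that to this ratio.
- Restricting the surface outcome to caries-active children is not a separate error in the economic formula. An arm's total is the same either way because caries-free children add zero; only a per-child mean changes.

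**Conclusion.** The sentence is wrong as written. It describes a cost per carious surface present, calls it a cost per surface avoided, and contradicts the incremental approach set out immediately before it. This holds under either reading of the cost term and needs no numerical assumption.

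The claim about direction is conditional. If costs are arm totals and part of them does not vary with surfaces, the written ratio rises as surfaces fall and can move opposite to the incremental ratio, as with 79 to 287 against 180 to 5 in the illustration. Those figures rest entirely on assumed costs and counts and show direction, not expected size.

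The effect is confined to a secondary economic measure. The main ICER is correctly specified, and the primary analysis and sample size do not depend on this sentence.

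**What to change.** Replace the last sentence of the Statistical analysis section with:

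> The incremental cost per carious surface avoided is the difference in mean discounted cost per child between arms (test minus control) divided by the difference in mean discounted number of carious surfaces per child (control minus test), with both means taken over all children analysed by randomised group and caries-free children counted as zero surfaces.

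This keeps the plan's 3.5% discounting of both costs and benefits and matches the form of the main ICER. The interval method, and the handling of children lost to follow-up, can be left to the analysis plan. The cost is one sentence of text, with no new data and no change to the trial's conduct. On the article's timetable, with recruitment from April 2011 and outcome examination at three years, it can be settled before outcome data exist.
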